## Abstract

**Background:**

Sarcopenic obesity (SO) is a complex condition characterized by the coexistence of sarcopenia and obesity, with pathophysiological mechanisms extending beyond the additive effects of either condition alone. Lifestyle intervention is considered an effective management strategy for SO; however, substantial interindividual variability in physiological status and behavioral preferences limits the implementation of personalized intervention. This study aims to evaluate the effectiveness of a knowledge graph-based lifestyle recommendation system in improving skeletal muscle mass and related outcomes in patients with SO.

**Methods:**

This randomized controlled trial will recruit 208 patients with SO, who will be randomly assigned in a 1:1 ratio to an intervention or control group. In addition to routine lifestyle guidance, the intervention group will receive a 24-week personalized intervention delivered through the Sarcopenic Obesity-Knowledge Graph Care System (SO-KGCS), whereas the control group will receive routine health education and lifestyle advice only. The intervention period is defined as the 24-week intervention period from baseline to week 24. The primary outcome measure is skeletal muscle mass. Secondary outcome measures include grip strength, skeletal muscle mass index, body fat percentage, physical function, and quality of life. Outcomes will be assessed at baseline before randomization and at weeks 8, 16, and 24 during the 24-week intervention period. The intervention will end at week 24, after which participants will enter a 24-week post-intervention follow-up period without systematic intervention. Follow-up outcome data will be collected at week 48.

**Discussion:**

This study will evaluate the effectiveness of a knowledge graph-based recommendation system in enhancing body composition, muscle strength, physical function, and quality of life in patients with SO. If effective, the SO-KGCS may provide a feasible intelligent approach for personalized chronic disease management.

**Trial registration:**

ChiCTR, ChiCTR2500111882.

## Introduction

Sarcopenic obesity (SO) is characterized by the coexistence of sarcopenia and obesity, representing a distinct clinical condition rather than a simple combination of the two disorders. The interaction between excess adiposity and impaired muscle mass or function increases the risk of adverse health outcomes. In 2022, the European Society for Clinical Nutrition and Metabolism (ESPEN) and the European Association for the Study of Obesity (EASO) published an expert consensus defining SO as a clinical and functional disorder characterized by increased body fat mass accompanied by reduced skeletal muscle mass or function [1]. Sedentary lifestyle, dysregulated fat metabolism, and metabolic changes associated with acute or chronic comorbidities are important contributors to the development of SO [2]. Research indicates that sarcopenia affects approximately 43% of overweight or obese women and 42% of overweight or obese men [3]. In the United States, the prevalence of SO was reported to be 8.1% among individuals aged 20–59 years and 28.3% among those aged ≥60 years. The prevalence further increased in the presence of metabolic abnormalities, reaching 19.7% in prediabetes, 34.5% in type 2 diabetes, and 25.4% in metabolic-associated fatty liver disease with fibrosis [4]. In a study involving 730 children and adolescents aged 4–14 years, using the muscle mass-to-fat mass ratio based on the third BMI quintile as the diagnostic cutoff (1.22 kg/kg for females and 1.35 kg/kg for males), the prevalence of SO was 9.3% in girls and 7.2% in boys [5].

The metabolic impact of SO exceeds that of sarcopenia or obesity alone. In SO, excess adipose tissue stores large amounts of fatty acids, promoting the accumulation of proinflammatory cells within adipose tissue and creating an inflammatory milieu that induces insulin resistance, mitochondrial dysfunction, and oxidative stress [6]. In skeletal muscle, these processes trigger inflammatory and oxidative stress responses, accelerate muscle protein degradation and myocyte apoptosis, and promote muscle catabolism and impaired regeneration, ultimately leading to sarcopenia. Muscle cell injury further reduces physical performance and physical activity, worsening obesity and establishing a vicious cycle that increases the risk of metabolic diseases and functional impairment [2]. SO significantly raises the risk of heart disease, metabolic syndrome, dementia, and postoperative complications. It also substantially elevates the risk of frailty, disability, and depression, with 2.7-fold and 2.9-fold higher risks of falls and disability, respectively [7–9], and a 24% increase in all-cause mortality [10]. Consequently, SO imposes a considerable burden on public health, families, and society. Once established, SO may persist throughout life, underscoring the importance of early recognition and intervention to reduce adverse metabolic outcomes. However, most patients with SO are diagnosed only after severe functional impairment caused by muscle loss has already occurred [11], resulting in missed opportunities for optimal early treatment.

Management of SO focuses on improving muscle mass while reducing excess adiposity. However, sarcopenia and obesity are currently treated as separate clinical conditions [10]. In elderly patients with SO, this separation creates challenges in dietary management because the need for increased protein intake may conflict with calorie restriction goals [12]. Similar challenges arise when combining resistance training to increase muscle mass with aerobic exercise aimed at fat reduction. In addition, substantial interindividual differences in physical condition, disease status, and metabolic rate make it difficult to design individualized dietary, nutritional, and exercise interventions. Effective management, therefore, requires collaboration among multiple professional teams, making clinical implementation complex and time-consuming.

Internet-based recommendation systems offer a novel strategy for personalized health interventions [13]. Health recommendation systems are specialized recommendation systems that provide users with personalized health information by automatically identifying and recommending appropriate content based on individual health conditions and needs [14]. In recent years, knowledge graph-based recommendation systems have been widely applied in domains such as movies, music, news, and product recommendations [15–17]. By incorporating knowledge graphs as auxiliary information, these systems effectively address the sparsity and cold-start limitations of traditional recommendation systems. Knowledge graph-based models can mine relational data and integrate it with existing user and item information, increasing data dimensionality and improving recommendation accuracy. Although recommendation systems have long been studied in healthcare, their application in SO management remains limited.

Based on this, we designed a randomized controlled trial to evaluate the effectiveness of a knowledge-graph-based care recommendation system in improving body composition, muscle strength, and physical function among patients with SO. We hypothesize that patients receiving this intelligent system-based intervention will achieve greater clinical benefits than those receiving standard care, thereby providing new evidence-based support and a feasible strategy for precision and intelligent management of chronic diseases in the elderly.

## Methods

### Study design

This single-blind, two-arm randomized controlled trial is designed to evaluate the effects of a knowledge graph-based lifestyle recommendation system on skeletal muscle mass, grip strength, skeletal muscle mass index, body fat percentage, physical function, and quality of life in patients with SO. Participants will be randomly assigned in a 1:1 ratio to either the intervention group or the control group. The intervention group will receive a 24-week lifestyle intervention aimed at increasing muscle mass and reducing weight, while the control group will receive conventional treatment and health education without personalized recommendations from the system. The total study duration is 48 weeks, comprising a 24-week intervention period followed by a 24-week follow-up period. Assessments will be conducted at baseline and at weeks 8, 16, 24, and 48, with week 24 marking the end of the intervention. Thereafter, both groups will enter a follow-up phase without systematic intervention and will be observed until week 48. The randomization sequence will be generated by a statistician using a computer-generated block randomization with block sizes of 4 or 6. Allocation concealment will be ensured through a password-protected centralized network system accessible only to independent registrars not involved in outcome assessment after completion of baseline assessments. Because of the nature of the lifestyle intervention, blinding of participants and intervention implementers is not possible. However, outcome assessors and statistical analysts will remain blinded throughout the study. All outcome assessments will be completed by uniformly trained independent assessors unaware of group allocation. Data managers and statistical analysts will remain blinded until database lock. Participants will be instructed not to disclose their group allocation to assessors, and an emergency unblinding procedure will be established if required. Intervention reporting will follow the Template for Intervention Description and Replication (TIDieR) checklist. The study protocol is developed in accordance with the SPIRIT statement (S1 File). Fig 1 and Fig 2 illustrate the proposed study timeline and procedures.

**Fig 1 pone.0353945.g001:**
[figure not shown]
Enrollment, interventions, and assessments schedule SMM, skeletal muscle mass; SMI, skeletal muscle index; SF-36, 36-item short form health survey.

**Fig 2 pone.0353945.g002:**
[figure not shown]
Study flow chart.

### Participants

Healthcare professionals will recruit participants through the Department of Endocrinology at Shenzhen Hospital (Futian) of Guangzhou University of Chinese Medicine. Recruitment announcements will be posted on local social media platforms (WeChat, TikTok, Xiaohongshu). In addition, primary care centers will distribute informational pamphlets, and meetings will be held with prospective participants.

### Inclusion criteria

Participants will be eligible if they meet all of the following criteria:

1) SO was diagnosed based on the concurrent presence of sarcopenia, obesity, and adequate baseline functional capacity [18]. Sarcopenia will be defined according to the Asian Working Group for Sarcopenia (AWGS) 2019 criteria, requiring low muscle strength alongside either reduced physical performance or low muscle mass. Low muscle strength will be defined as handgrip strength <28 kg for men and <18 kg for women. Reduced physical performance or low muscle mass will be defined as a Short Physical Performance Battery (SPPB) score ≤9, or an appendicular skeletal muscle mass index (ASMI) <7.0 kg/m^2^ in men and <5.4 kg/m^2^ in women, assessed using dual-energy X-ray absorptiometry (DXA) [19]. Obesity will be defined as either a body mass index (BMI) ≥28 kg/m^2^ or a body fat percentage >25% in men and >30% in women, measured using the InBody 770 device [20].2) Age ≥ 60 years;3) Ability to safely participate in the intervention;4) Willingness to undergo study assessments and provision of written informed consent voluntarily.

### Exclusion criteria

Participants meeting any of the following criteria will be excluded:

1) Acute myocardial infarction, unstable angina, stroke, heart failure, or other severe cardiovascular or cerebrovascular diseases that preclude participation in exercise training or physical function assessments;2) Severe hepatic or renal insufficiency, uncontrolled severe endocrine disorders, active malignancy, or current receipt of radiotherapy;3) Diabetes mellitus;4) Severe psychiatric disorders, cognitive impairment, or any other condition that would impair compliance with the intervention or follow-up;5) Severe osteoarticular disease causing marked limitation of motor function;6) Current participation in another clinical trial.

### Discontinuation of the intervention and withdrawal from the study

Participants may discontinue the intervention or withdraw from the study at any time. Discontinuation of the intervention will not be regarded as withdrawal from the study unless the participant explicitly requests withdrawal or declines further follow-up. Participants who discontinue the intervention will be encouraged to complete all scheduled follow-up assessments whenever possible. The intervention may be temporarily suspended or permanently discontinued at the investigator’s discretion under any of the following circumstances:

1) occurrence of a serious adverse event, an adverse event considered related to the intervention, or any other condition that makes continued intervention unsafe;2) significant deterioration in key health indicators or the development of clinical conditions that make continued intervention inappropriate;3) persistent inadequate adherence despite reminders and assessment of possible causes, defined as weekly adherence of <50% for two consecutive weeks or overall adherence of <50% during the study period;4) inability to understand or follow the intervention recommendations or a newly identified or previously undisclosed medical condition that may compromise intervention safety;5) a request by the participant to discontinue the intervention or withdraw from the study.

For participants who discontinue the intervention or withdraw from the study, investigators will make reasonable efforts, with the participant’s consent, to document the reason for and date of discontinuation or withdrawal and to complete feasible safety and outcome assessments. Appropriate clinical management will be provided if discontinuation is related to adverse events, deterioration in health status, or unsatisfactory treatment effects.

All available data collected before discontinuation or withdrawal will be included in the analysis unless the participant withdraws consent for data use. No replacement participants will be recruited. All randomized participants will be analyzed according to the intention-to-treat (ITT) principle, regardless of intervention discontinuation, protocol deviations, or adherence level. Protocol deviations, unresolved data-quality issues, and adherence-related issues will be documented and considered in sensitivity or per-protocol analyses, as appropriate.

### Sample size

The sample size was calculated using G-power 3.1 software. The calculation was based on a two-sided comparison of the mean change in skeletal muscle mass (SMM) between the two groups, with SMM prespecified as the sole primary confirmatory outcome. The expected effect size was derived from a previous Internet-based nutrition and exercise intervention study in older adults with sarcopenia [21]. In that study, the mean change in SMM was −0.10 kg in the control group and 1.09 kg in the comprehensive intervention group, corresponding to a between-group difference of 1.19 kg. Because the standard deviation of the SMM change score was not directly reported, it was conservatively estimated from the reported baseline and post-intervention standard deviations, assuming a pre-post correlation coefficient of 0.50. This yielded an estimated pooled standard deviation of approximately 2.70 kg and a Cohen’s d of approximately 0.44. Although the proposed intervention incorporates a knowledge graph-based recommendation system that may enhance intervention individualization, this moderate effect size was adopted to avoid overestimating the intervention effect. With a two-sided α level of 0.05, power of 0.80, and a 1:1 allocation ratio, 83 participants were required per group. Factoring an anticipated dropout rate of 20%, 104 participants will be enrolled in each group, resulting in a total sample size of 208 participants.

### Procedure

Potential participants will first undergo screening to determine eligibility, including assessment of medical history and lifestyle habits. Individuals meeting the eligibility criteria will be invited to an in-person visit, during which the study procedures will be explained and written informed consent will be obtained.

All baseline assessments will be completed on a single day following participant enrolment. Upon arrival at the hospital, participants will complete questionnaires collecting demographic and clinical information, including sex, age, height, weight, marital status, home address, and contact information. Body composition measurements and physical fitness tests will then be performed to assess mobility, muscle strength, and overall physical function. Participants will also complete supplementary questionnaires at home covering dietary status, quality of life, and SO-related symptoms.

After baseline assessment, trained research staff will assist participants in the intervention group with downloading and using the SO-KGCS system. Based on baseline assessment results, the system will provide personalized plans for nutrition, exercise, and lifestyle modification. Participants in the intervention group will receive regular personalized updates through the system, while those in the control group will receive standard health education. The intervention period will last 24 weeks. During the study, all participants will be instructed to maintain a daily calorie intake approximately 200 kcal below their baseline levels, in accordance with the ESPEN and EASO Consensus Statement on SO. Daily protein intake will be maintained at ≥1.2 g/kg body weight.

All assessments will be performed by uniformly trained professional nurses using standardized procedures. After baseline assessment and randomization at week 0, outcome assessments will be conducted at weeks 8, 16, and 24, with week 24 defined as the end of the intervention. A final follow-up assessment will be conducted at week 48, corresponding to 24 weeks after completion of the intervention. Adherence, adverse events, and reasons for withdrawal will be recorded throughout the intervention period.

### Randomization and blinding

Participants will be randomized in a 1:1 ratio to the intervention or control group using a computer-generated block randomization sequence prepared by an independent statistician, using random blocks of 4 or 6 to prevent prediction of assignment. Allocation concealment will be maintained through a password-protected centralized web-based system accessible only to an independent registrar after completion of baseline assessments. Because of the nature of the personalized lifestyle intervention, participants and intervention providers cannot be blinded. However, outcome assessors and statisticians will remain blinded throughout the study. Outcome assessments will be completed by standardized independent assessors unaware of group allocation. Participants will be instructed not to disclose their group allocation to assessors. Intervention providers will not participate in outcome assessments. An emergency unblinding protocol supervised by the Ethics Committee will also be established to address potential safety risks.

### Intervention

#### Control group intervention.

Participants in the control group will receive a routine lifestyle intervention. Following hospital discharge or outpatient visits, each participant will receive an SO lifestyle management handbook and verbal guidance on basic SO management in older adults, including the risks associated with sarcopenia and obesity, dietary recommendations such as increasing protein intake and reducing high-fat and high-sugar foods, exercise advice including daily 30-minute walks and simple limb activities, and chronic disease management measures such as ensuring adequate sleep and monitoring blood pressure and blood glucose levels.

### Experimental group

#### Preliminary preparation.

A systematic search was conducted across multiple databases and relevant websites, including BMJ Best Practice, UpToDate, the Joanna Briggs Institute (JBI, Australia), the Center for Evidence-Based Healthcare, the Guidelines International Network (GIN), the Cochrane Library, OVID, PubMed, Web of Science, the European Society for Clinical Nutrition and Metabolism, the Academy of Nutrition and Dietetics, the Society for Parenteral and Enteral Nutrition, MedLink, the China Biomedical Literature Service Network, CNKI, Wanfang, and VIP, to retrieve lifestyle-related content concerning SO. The search period extended from database inception to August 1, 2025. Based on the retrieved literature, the research team developed a preliminary lifestyle intervention plan for SO. Following expert review and revision by a multidisciplinary panel of 10 endocrinologists, nurses, and nutritionists, and considering Chinese national conditions and patient needs, the final intervention plan and knowledge graph were established (Fig 3).

**Fig 3 pone.0353945.g003:**
[figure not shown]
Knowledge Map of SO.

The knowledge map integrates multidimensional information such as disease characteristics, nutritional requirements, exercise modalities, traditional Chinese medicine (TCM) interventions, and lifestyle factors, thereby forming a structured intervention knowledge base to support personalized recommendations.

#### Intervention implementation.

In addition to the routine lifestyle guidance for SO, participants in the intervention group will be instructed to use the Sarcopenic Obesity-Knowledge Graph Care System (SO-KGCS) for personalized lifestyle intervention. SO-KGCS is a mobile application developed specifically for patients with SO. Built on a knowledge graph framework, the system integrates multisource data to identify patterns of coexisting low muscle mass and excess fat accumulation, and generates personalized nutrition, exercise, and lifestyle recommendations aimed at simultaneous fat reduction and muscle gain. After logging in, participants will enter the treatment advice interface and complete personal information, including demographic characteristics, functional indicators, physiological and biochemical parameters, medical history, medication history, and lifestyle habits. Based on these data, the system will automatically generate a personalized intervention plan comprising disease assessment, treatment objectives, exercise training, dietary modification, TCM interventions, lifestyle optimization, and necessary medical recommendations, together with expected outcomes and precautions. The feedback section will allow patients to report their experiences, enabling medical staff to adjust recommendations when necessary. Participants will be required to follow the recommended lifestyle modifications and regularly report their progress through the platform. The system interface is shown in Fig 4.

**Fig 4 pone.0353945.g004:**
[figure not shown]
Knowledge Graph-Based Recommendation System.

To ensure intervention fidelity and minimize confounding, permitted and prohibited concomitant treatments during the study period have been defined. Participants may continue stable existing medications and receive necessary emergency care. However, participation in other structured programs targeting weight loss, muscle gain, or physical function improvement, as well as unauthorized use of medications affecting muscle metabolism or body composition, will be prohibited. Compliance will be monitored through regular follow-up, and all relevant events will be documented and considered in the analysis.

### Strategies to improve intervention adherence

To enhance intervention adherence, the research team will provide close monitoring, regular targeted clinical guidance, biweekly follow-up visits, and supportive education through mobile applications. Family members or other individuals within the participant’s social network will also be involved at study initiation to support recommended lifestyle modifications. To improve data completeness and maintain long-term follow-up validity, several strategies will be implemented, including obtaining informed consent for long-term follow-up at enrollment, reducing participant burden through optimized procedures such as telephone follow-up and online questionnaires, maintaining engagement through regular health newsletters and appropriate incentives, and establishing a multi-channel contact mechanism with backup contact information to track participants lost to follow-up. Appropriate statistical methods will be used to manage and report missing follow-up data.

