### Adverse events

All adverse events occurring during the study will be recorded and monitored. Data will be collected on falls, injuries, musculoskeletal problems, hypoglycemic episodes, major cardiovascular disease events, and any other events potentially related to the study procedures or interventions. All adverse events will be carefully evaluated and followed until symptoms or signs resolve or stabilize. Detailed records of management measures and outcomes will be maintained. Follow-up methods will be selected according to event severity and may include inpatient observation, outpatient follow-up, home visits, telephone follow-up, or written communication.

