Prespecified exploratory subgroup analyses will be performed by age and sex through inclusion of group-by-time-by-subgroup interaction terms in the linear mixed-effects model. Model assumptions will be evaluated using residual plots, normal Q-Q plots, and outlier diagnostics. If substantial heteroscedasticity or deviation from residual non-normality is detected, robust standard errors will be used in sensitivity analyses while retaining the primary model structure. Safety analyses will be primarily descriptive. Adverse events and serious adverse events will be summarized by group, severity, possible relationship to the intervention, and outcome. All statistical tests will be two-sided, and *P* < 0.05 for the primary outcome will be considered statistically significant. Statistical analyses will be performed using R software, version 4.4.2 (R Foundation for Statistical Computing, Vienna, Austria).

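### The by-group adverse event summary is open to detection bias for mild, self-reported events, because contact appears more frequent in the intervention arm and no common way of asking is stated

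*Protocol article*

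**What the plan says.** - **Extra contact.** Strategies to improve intervention adherence: "To enhance intervention adherence, the research team will provide close monitoring, regular targeted clinical guidance, biweekly follow-up visits". The arm is not named. A separate sentence in that section lists telephone follow-up, online questionnaires and backup contacts. Their purpose is complete data, and they are not tied to an arm.
- **App, intervention arm only.** Intervention implementation: "Participants will be required to follow the recommended lifestyle modifications and regularly report their progress through the platform". Also: "The feedback section will allow patients to report their experiences, enabling medical staff to adjust recommendations when necessary".
- **Controls.** Control group intervention: "each participant will receive an SO lifestyle management handbook and verbal guidance on basic SO management in older adults". No contact schedule between assessments is given.
- **Contacts common to both arms.** Procedure: "outcome assessments will be conducted at weeks 8, 16, and 24, with week 24 defined as the end of the intervention". One further assessment follows at week 48.
- **AE collection.** Adverse events: "All adverse events occurring during the study will be recorded and monitored". This is not limited to one arm. The section names falls, injuries and musculoskeletal problems first. It states no schedule or method of asking that is shared by both arms.
- **AE analysis.** Statistical analysis: "Adverse events and serious adverse events will be summarized by group, severity, possible relationship to the intervention, and outcome". The safety analysis is described as mainly descriptive, and no AE test is named.

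**The concern.** Whether a minor fall, strain or joint complaint gets recorded depends on whether someone asks and how long ago it happened. If staff see one arm every two weeks and also read its app reports, while the other arm is sure to be seen only every eight weeks, the first arm will tend to have more such events on file even when true harm is equal.

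A by-group AE table is read as a comparison whether or not it carries a test. Two errors are possible. The system could look harmful when it is not, or a real excess of exercise-related injury could be explained away as closer observation. Participants and intervention providers are also unblinded, so events that surface through the extra contacts come through unblinded channels, whereas assessors at the common visits are to be unaware of allocation. The Discussion says the study emphasizes safety, so the table will be relied on.

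**Working it through.** **The plan's own figure.** There is none to reproduce: the article gives no AE rate, AE power or AE sample size.

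**Step 1: contacts over the 24-week intervention, if biweekly visits are for the intervention arm only.**
- Intervention arm: 24 / 2 = up to 12 visits, plus app reports.
- Control arm: 24 / 8 = 3 assessments (weeks 8, 16 and 24).
- Ratio of contact frequency: 12 / 3 = 4.

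**Step 2: what that could do to recorded events.** All of the following are assumptions, not statements in the documents:
- True event rates are equal in the two arms.
- Events fall evenly within each interval between contacts.
- Events are asked about at each contact and recorded only then.
- Recall decays exponentially with half-life h weeks.

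The average share of events still recalled, with contact every L weeks, is

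f(L) = (1 − 2^(−L/h)) / (ln 2 × L/h).

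For h = 4:
- f(2) = (1 − 2^(−0.5)) / (0.693 × 0.5) = 0.845
- f(8) = (1 − 2^(−2)) / (0.693 × 2) = 0.541
- Ratio: 0.845 / 0.541 = 1.56

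| Assumed half-life (weeks) | f(2) | f(8) | Recorded ratio, intervention / control |
|---|---|---|---|
| 2 | 0.721 | 0.338 | 2.13 |
| 4 | 0.845 | 0.541 | 1.56 |
| 8 | 0.918 | 0.721 | 1.27 |
| 16 | 0.958 | 0.845 | 1.13 |
| 26 | 0.974 | 0.901 | 1.08 |

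The two outer rows show how strongly the answer follows the assumption. The range used here is 4 to 16 weeks.

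**Step 3: the same on the scale of the table.** Assume a true 24-week risk of 20% in both arms and Poisson events, so λ = −ln(0.8). The share of participants recorded with an event is 1 − exp(−λ f(L)).
- h = 4: 17.2% versus 11.4%, or about 17.9 versus 11.8 of 104 participants per arm.
- h = 16: 19.2% versus 17.2%, or about 20.0 versus 17.9 of 104.

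**Step 4: the other reading.** If both arms have biweekly visits, L = 2 in both and the ratio from visits is f(2) / f(2) = 1. Only the app then differs. The documents give nothing from which to size that part.

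**The case against.** The strongest reply is that much of the asymmetry is inferred.

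- **The arm is not named.** A reader might take it as settled that only the intervention arm has biweekly visits. The article does not say so. The heading, the adherence purpose and the lack of any interim schedule for controls make it the natural reading, no more. The app asymmetry is explicit.
- **Elicitation is not described.** A reader might also infer that one arm is asked about AEs every two weeks and the other every eight. No section says AEs are asked about at the biweekly visits, or that controls are asked only at assessments. The app's feedback section is for experiences with the recommendations and is not called an AE channel. The rule on recording AEs covers both arms. This stands, so the summary is open to bias rather than shown to be biased.
- **No formal comparison is planned.** The safety analysis is a by-group description without a test. This stands as to wording, but a descriptive table still invites comparison.
- **A shared AE form may sit in the full protocol, which the article condenses.** It may, and the absence of that form here is not the finding. The finding is that the stated contact pattern and the by-group table do not fit together unless events are asked about equally.
- **The ratios have no basis in the documents.** Correct: they are illustrations and cannot be read as the trial's expected bias.
- **Restricting the table to common visits could hide real harms.** This stands and shapes the fix.

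**Conclusion.** The point holds in a limited form. The by-group AE summary is open to detection bias for mild, self-reported events, in the direction of more recorded events in the intervention arm. This rests on one explicit asymmetry (the app) and one probable asymmetry (the biweekly visits), with no stated equal way of asking.

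The size cannot be fixed from the documents. With contact every 2 versus every 8 weeks, events elicited at those contacts and recall half-lives of 4 to 16 weeks, the spurious ratio is about 1.6 to 1.1. It is lower if both arms have biweekly visits.

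It would go too far to conclude that the AE table can support no safety conclusion. Serious events depend much less on how often people are asked. The primary outcome, skeletal muscle mass, is measured at the same scheduled assessments in both arms and is unaffected, as is the sample size.

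**What to change.** 1. State whether the biweekly visits apply to both arms.
2. At weeks 8, 16, 24 and 48, put the same scripted AE questions to every participant in both arms: falls, injuries, musculoskeletal problems, hypoglycaemia, cardiovascular events and other. Cover all the time since the last common visit.
3. Base the main by-group AE table on the events elicited there.
4. Also report all AEs from any source by group, marking those found only through the app or a biweekly visit, so that no harm is dropped.

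The cost is one short form at visits that already take place, one extra table and a line in the analysis text. With the same questions at the same times, the ratio in the model above is f(8) / f(8) = 1. Some difference may remain, because a participant who has already discussed an event at a biweekly visit may recall it better later. The trial is recruiting, and minor events missed now cannot be reliably recovered, so the change is best made soon.
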